|                             | 
3-1. Visit 3 (Week 0): the following procedures will be performed: pregnancy test (urine hCG: only for women of childbearing potential), assignment of allocation number, dispensing of the IPs and training on the method of administration, checking for concomitant medications and AEs, and TLC training
 
3-2. Visit 4 (Week 12): the following procedures will be performed: vital signs (blood pressure and pulse rate) measurement, physical examination, body weight measurement, a pregnancy test (urine hCG: only for women of childbearing potential), laboratory tests (hematology, blood chemistry, urinalysis, thyroid function test, and lipid parameters), and ECG (if necessary); collection of returned drugs and treatment compliance assessment, checking for concomitant medications and AEs, and TLC training
                                                                                                                                                                                                                                                                                                                                                                                                                                                                                                                                                                                                                                                                                                                                                                                                                                                                                                                                                                                                                                                                                                                                                                                                                                                                                                                                                                                                                                                                                                                                                                                                                                                                                                                                                                                                                                                                                                                                                                                                                                                                                                                                                                                                             |
| Endpoints            | 
 
▶ Efficacy               
 
1. Primary efficacy endpoint: Percent change in LDL-C at Week 12 from baseline
 
2. Secondary efficacy endpoints:                   
 
1) Percent changes in lipid parameters at Week 12: LDL-C, HDL-C, TG, total cholesterol, Apo-A1, Apo-B, non-HDL-C/HDL-C ratio, total cholesterol/HDL-C ratio, LDL-C/HDL-C ratio, Apo-B/Apo-A1 ratio
 
2) Changes in HbA1c and glucose at Week 12
 
3) Percentage of subjects achieving the target LDL-C by risk group
 
4) Percentage of subjects achieving the target non-HDL-C by risk group
 
 
 
3. Exploratory endpoint: Pharmacoeconomics
 
 
 
▶ Safety
AEs, vital signs, laboratory tests, etc.
 
                                                                                                                                                                                                                                                                                                                                                                                                                                                                                                                                                                                                                                                                                                                                                                                                                                                                                                                                                                                                                                                                                                                                                                                                                                                                                                                                                                                                                                                                                                                                                                                                                                                                                                                                                                                                                                                                                                                                                                                                                                                                                                                                                                                            |
| Statistical Analysis | 
 
▶ General Principles of Analysis
All statistical analyses in this study will be performed with a two-sided test at a significance level of 5%. If any missing value is found in the efficacy data, the efficacy analysis will be performed applying the last observation carried forward (LOCF), and the analysis of the safety data will be performed using raw data without applying the LOCF.
 
▶ Demographic Information and Other Pre-Treatment Characteristics
The subject's demographic information and pre-treatment characteristics of the IP will be summarized and analyzed by treatment group for the full analysis set (FA Set). For continuous data such as age, descriptive statistics (mean, standard deviation, median, minimum, and maximum) will be presented and the independent samples t-test will be performed for comparison between the treatment groups. For categorical data such as gender and age group, the number and percentage (%) of subjects will be presented and the chi-square test or the Fisher's exact test will be performed for comparison between the treatment groups.

Concomitant medications will be classified into prior medications (administration started before the IP administration) and concomitant medications (administration started after the IP administration) and coded using the WHO-ATC Index. The number and percentage (%) of subjects by 1st level of the WHO-ATC Index will be presented, and the chi-square test or the Fisher's exact test will be performed for comparison between the groups.

In addition, medical history will be coded using MedDRA version 20.0. The number and percentage (%) of subjects by System Organ Class (SOC) will be presented, and the chi-square test or the Fisher's exact test will be performed for comparison between the groups.
 
▶ Analysis of the Efficacy Endpoints
The efficacy endpoints will be analyzed with the FA Set as the primary analysis set and the Per Protocol Set (PP Set) as the secondary analysis set.               
 
1. Primary efficacy endpoint
The mean percent change from baseline in LDL-C at Week 12 will be compared between the study group and the control group, and to demonstrate that LDL-C lowering effect in the study group is superior to that in the control group, the independent samples t-test or the Wilcoxon rank sum test will be performed.
 
2. Secondary efficacy endpoints                   
 
1) The mean percent changes from baseline in lipid parameters at Week 12 will be compared between the study group and the control group using the independent samples t-test or the Wilcoxon rank sum test.
 
 
 
 
* Lipid parameters: HDL-C, TG, total cholesterol, Apo-A1, Apo-B, non-HDL-C/HDL-C ratio, total cholesterol/HDL-C ratio, LDL-C/HDL-C ratio, Apo-B/Apo-A1 ratio
 
 
 |

- 2) The mean change from baseline in HbA1c and glucose at Week 12 will be compared between the study group and the control group using the independent samples t-test or the Wilcoxon rank sum test.
- 3) The percentage of subjects achieving the target LDL-C by risk group at Week 12 after administration will be set as follows and compared between the study group and the control group using the chi-square test or the Fisher's exact test.
  - Achievement of LDL-C in high-risk group: Percentage (%) of subjects achieving LDL-C < 100 mg/dl
  - Achievement of LDL-C in very high-risk group: Percentage (%) of subjects achieving LDL-C < 70 mg/dl
- 4) The percentage of subjects achieving the target non-HDL-C by risk group at Week 12 after administration will be set as follows and compared between the study group and the control group using the chi-square test or the Fisher's exact test.
  - Achievement of non-LDL-C in high-risk group: Percentage (%) of subjects achieving non-HDL-C < 130 mg/dl
  - Achievement of non-LDL-C in very high-risk group: Percentage (%) of subjects achieving non-HDL-C < 100 mg/dl
3. Exploratory objective  
To evaluate pharmacoeconomics of the study group, an average cost effectiveness ratio (ACER) will be calculated for the percent change from baseline in LDL-C at Week 12 to determine how much cost is added or saved per unit of an improved effect of the study group compared to the control group.
- Analysis of Safety Endpoints
  1. Adverse event  
Adverse events that occur after administration of the IP will be coded using MedDRA version 20.0. The number of subjects and incidence (%) will be presented by SOC, and the chi-square test or the Fisher's exact test will be performed for comparison between the groups. The AEs that occur in the subjects will be classified into adverse drug reactions (ADRs), serious adverse events (SAEs), and serious adverse drug reactions (SADRs) and analyzed in the same way.  
  
In addition, for unexpected AEs that are not reflected in the labeled information, the number of subjects and incidence (%) will be presented by SOC and Preferred Terms (PT), and the chi-square test or the Fisher's exact test will be performed for comparison between the groups. As with the analysis of the AEs, unexpected AEs will be classified into ADRs, SAEs, and SADRs and analyzed in the same way.
  2. Vital signs  
Descriptive statistics will be presented by time point, and change from baseline at Week 12 after administration will be compared between the treatment groups using the independent samples t-test or the Wilcoxon rank sum test. The comparison within the treatment group will be performed using the paired samples t-test or Wilcoxon signed rank test.
  3. Laboratory tests  
The number and percentage (%) of subjects determined to be clinically significant abnormal based on laboratory test results will be presented by treatment group, and comparison between before and after administration will be performed using the McNemar test, and comparison between the treatment groups will be performed using the chi-square test or the Fisher's exact test.

## 2 Title and Phase of the Study

- A. Title: A Randomized, Open-label, Parallel, Multi-Center Phase IV study to Compare of the efficacy and safety of Lipilou 20 mg and Lipilou 10 mg in high-risk patients with hypercholesterolemia (PEARL study)
- B. Phase: Phase IV study

## 3 Introduction

### 3.1 Background

Dyslipidemia, which is a disease caused by metabolic disorder of lipoprotein, refers to a condition where total cholesterol, LDL-cholesterol, and triglyceride in blood are increased from the reference value or HDL-cholesterol in blood is decreased from the reference value. Dyslipidemia itself does not cause particular symptoms, but if left untreated, cholesterol builds up on the lining of the blood vessels and inflammatory response is caused, leading to formation of plaques around the inflamed area. As a consequence, it causes atherosclerosis, narrowing of the blood vessels. Moreover, if atheromatous plaques become larger in blood vessels with small inner diameter such as carotid artery, which supplies blood to the brain, or coronary artery, which supplies blood to the heart muscles, the risk of vascular stenosis or occlusion increases significantly. When vascular stenosis occurs, symptoms of ischemia first occur in hypoxia-sensitive organs. Ultimately, atherosclerosis causes ischemic cerebrovascular diseases such as cerebral infarction and ischemic heart diseases such as angina pectoris or myocardial infarction.

With regard to the treatment of such dyslipidemia, NCEP ATP III guideline specifies that LDL-C should be controlled primarily for dyslipidemia and that LDL-C treatment goal for the very-high risk group per the risk group classification should be LDL-C < 70 mg/dL at most. The 2013 American College of Cardiology (ACC)/American Heart Association (AHA) Guideline on Dyslipidemia recommends using the percent reduction in LDL-C as an indication of response and adherence to statin therapy instead of the recommendation for LDL-C treatment targets and aims to lower LDL-C by up to  $\geq 50\%$  as the guideline on the treatment of blood cholesterol to reduce the risk of atherosclerotic cardiovascular diseases (ASCVDs) in adults. Ultimately, the treatment of dyslipidemia is aiming at lowering LDL-C more intensely.

Atorvastatin, a typical treatment used for dyslipidemia, inhibits HMG-CoA reductase, which is the enzyme that acts on the process of converting HMG-CoA into mevalonic acid, in the rate-limiting step of cholesterol synthesis. This reduces the production of cholesterol in the liver cells, which causes a decreased amount of cholesterol within the cells. As a result, the expression of LDL receptors on the liver cell surface is increased, which in turn greatly reduces cholesterol in the blood and lower the concentration of serum cholesterol.

Commercially available atorvastatin varies in dose, but there are not many researches done to study the cost-effective aspect of different doses, and in Korea, there is a tendency of using atorvastatin 10 mg as the first-line treatment more than atorvastatin 20 mg. A study conducted in Korean dyslipidemia patients demonstrated administration of atorvastatin 20 mg for a daily dose of statin as a first-line treatment as the most successful profile in lowering the LDL-C level to an ideal level, unless high-risk Korean patients have a very high baseline LDL-C level of > 160 mg/dL. This result becomes more concrete when the analysis was performed considering the effect as well as the cost, and administration of atorvastatin 20 mg a day is relatively most cost-effective.

Chong Kun Dang Pharmaceutical Corp. intends to provide a beneficial drug to high-risk patients with dyslipidemia by demonstrating that Lipilou 20 mg is more reasonable and cost-effective than Lipilou 10 mg particularly in high-risk patients who need a long-term statin therapy and that there is no significant difference in the incidence of adverse events (AEs), based on comparison between Lipilou 10 mg and 20 mg, atorvastatin agents.

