## 4 Study Objective

Only the subjects who meet the inclusion/exclusion criteria will be randomized to either 1 tablet of the study drug (Lipilou 20 mg) or 1 tablet of the control drug (Lipilou 10 mg) and take the doses for 12 weeks for the following objectives.

- A. Primary objective:  
To evaluate the percent change from baseline in LDL-C at Week 12
- B. Secondary objectives:
  - ① To evaluate the percent changes from baseline in lipid parameters at Week 12
  - ② To evaluate the changes from baseline in HbA1c and glucose at Week 12
  - ③ To evaluate the percentage of subjects achieving the target LDL-C by risk group
  - ④ To evaluate the percentage of subjects achieving the target non-HDL-C by risk group
  - ⑤ To evaluate the safety based on AEs, vital signs, laboratory tests, etc.
- C. Exploratory objective:  
To evaluate pharmacoeconomics of Lipilou 20 mg and 10 mg at Week 12 from baseline

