### 11.2 Statistical Analysis Method

#### 11.2.1 General Principles of Analysis

All statistical analyses in this study will be performed with a two-sided test at a significance level of 5%. If any missing value is found in the efficacy data, the efficacy analysis will be performed applying the last observation carried forward (LOCF), and the analysis of the safety data will be performed using raw data without applying the LOCF.

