#### 11.2.5 Statistical Analysis of Safety Data

The safety endpoints will be analyzed on the safety analysis set.

- 1) Adverse event (AE)
 

AEs will be coded using MedDRA version 20.0. The number of subjects and incidence (%) will be presented by SOC, and the chi-square test or the Fisher's exact test will be performed for comparison between the groups. The AEs that occur in the subjects will be classified into ADRs, SAEs, and SADR and analyzed in the same way.

In addition, for unexpected AEs that are not reflected in the labeled information, the number of subjects and incidence (%) will be presented by SOC and Preferred Terms (PT), and the chi-square test or the Fisher's exact test will be performed for comparison between the groups. As with the analysis of the AEs, unexpected AEs will be classified into ADRs, SAEs, and SADR and analyzed in the same way.
- 2) Vital signs
 

For vital signs results, descriptive statistics will be presented by time point, and change will be compared between the treatment groups using the independent samples t-test or the Wilcoxon rank sum test. The comparison within the treatment group will be performed using the paired samples t-test or Wilcoxon signed rank test.
- 3) Laboratory tests
 

The number and percentage (%) of subjects determined to be clinically significant abnormal based on laboratory test results will be presented by treatment group, and comparison between before and after administration will be performed using the McNemar test, and comparison between the treatment groups will be performed using the chi-square test or the Fisher's exact test.

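### Section 3.1 aims to demonstrate no significant difference in adverse events between doses, but the only AE comparison the protocol fixes is a low-power significance test that cannot support that aim

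*Protocol*

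**What the plan says.** Protocol section 3.1 (Background) closes with what the sponsor means to show. One part is that 20 mg is the more reasonable and cost-effective dose. The other is that "there is no significant difference in the incidence of adverse events (AEs), based on comparison between Lipilou 10 mg and 20 mg". The verb governing both parts is demonstrating.

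The formal safety objective is neutral. Section 4 reads "To evaluate the safety based on AEs, vital signs, laboratory tests, etc", and the synopsis objective says the same in substance.

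For the AE analysis, section 11.2.5 states "The number of subjects and incidence (%) will be presented by SOC, and the chi-square test" or Fisher's exact test will compare the groups, repeated for ADRs, SAEs and SADRs. The synopsis repeats this. Section 11.2.1 sets every test at two-sided 5%. Preferred terms are named for one subset only: "for unexpected AEs that are not reflected in the labeled information, the number of subjects and incidence (%) will be presented by SOC" and by preferred term.

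Section 11.4 derives the sample size from the LDL-C difference alone. The protocol states no safety margin, no equivalence or non-inferiority hypothesis and no interval for an AE difference.

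**The concern.** A chi-square or Fisher test asks whether the data contradict equal incidence. If they do not, either the incidences are close or the trial was too small to tell them apart, and the p-value does not say which. When the stated aim is to demonstrate the absence of a significant difference, a smaller sample makes the aim easier to reach, whatever the true risks are.

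At stake is the safety half of the sponsor's intended message, that the higher dose brings more benefit with no difference in AEs. Under the plan as written, that half would rest on low power and not on evidence of closeness. The Background and the formal objectives also disagree on what the trial is meant to establish about safety. The primary LDL-C conclusion is not affected.

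**Working it through.** **1. The plan's own figure.** Section 11.4 uses a difference of −6, SD 13, two-sided 5% and 90% power:

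n = 2 × (1.96 + 1.28)² × 13² / 6² = 98.56, so 99 per group; 99 / 0.8 = 123.75, so 124 per group and 248 in total.

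This reproduces. It is a calculation for LDL-C and says nothing about AE incidence.

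**2. Inputs for the AE comparison.** n = 124 per arm (section 11.4; allocation 1:1, section 6.2.1). This is the most the safety set of section 11.1.3 can contain at the planned enrolment, because a subject must take at least one dose. The level is two-sided 5% (section 11.2.1). The AE rates p₁ (10 mg) and p₂ (20 mg) are assumptions, since the protocol gives none, so a range is shown.

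**3. Formula.** With p̄ = (p₁ + p₂)/2, the normal approximation with pooled variance under the null is

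power = Φ{ [ (p₂ − p₁) − 1.96 √(2 p̄(1 − p̄)/n) ] / √( [p₁(1 − p₁) + p₂(1 − p₂)]/n ) }.

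Worked case, 5% versus 10%: p̄ = 0.075. The null term is 1.96 × √(2 × 0.075 × 0.925/124) = 0.0656. The denominator is √((0.0475 + 0.09)/124) = 0.0333. Power = Φ((0.05 − 0.0656)/0.0333) = Φ(−0.467) = 0.32, so the test is non-significant 68% of the time.

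**4. Chance of a non-significant test although the true risk is higher on 20 mg (124 per arm).**

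| Assumed true rates | Ratio | Normal approximation | Fisher's exact (full enumeration) |
|---|---|---|---|
| 2% vs 4% | 2 | 85% | 93% |
| 5% vs 10% | 2 | 68% | 77% |
| 10% vs 20% | 2 | 40% | 47% |
| 10% vs 15% | 1.5 | 78% | 83% |
| 20% vs 30% | 1.5 | 56% | 61% |

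Full enumeration of the uncorrected chi-square test gives 87%, 68% and 39% for the three doublings, close to the approximation.

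The weakness has limits. A doubling from 20% to 40% would be missed only 6.5% of the time. The problem therefore lies with less common events and with moderate increases in common ones. For 80% power, a 5% rate would have to rise to about 16%, and a 10% rate to about 23%.

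**5. What an interval would show.** With equal true rates, the 95% half-width for the risk difference is 1.96 √(2p(1 − p)/124): ±3.5 points at 2%, ±5.4 at 5%, ±7.5 at 10% and ±10.0 at 20%. At 10%, for example, 1.96 × √(0.18/124) = 0.075. A reader given that interval can see which differences remain possible; a bare p-value hides them.

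**6. Whether a formal claim is within reach.** Take one-sided 2.5%, 80% power, equal rates of 10% and an illustrative 5-point margin: n = (1.96 + 0.84)² × 2 × 0.10 × 0.90 / 0.05², about 566 per arm. With a 10-point margin it is 142 per arm. Both exceed 124. The margins are for illustration only; the protocol sets none.

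**The case against.** The strongest reply is that the sentence stands in the Background as an intention, while both statements of the formal safety objective are neutral and the only hypothesis in the protocol concerns LDL-C. Sizing a trial on its primary endpoint is usual, and descriptive AE counts with routine tests are not wrong in themselves. All of this stands, and it limits the point to the stated aim and the analysis meant to serve it.

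A reader might go further and infer that the protocol treats p > 0.05 as proof that the doses are equally safe. The document does not support that. No section gives a rule for reading a non-significant AE test, and section 3.1 does not speak of equality. What can be said is narrower: the protocol states an aim of demonstrating no significant difference and fixes only one kind of comparison that could serve it.

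A reader might also infer that labelled events can be seen only inside organ-class totals. That is too absolute. Section 10.4.1 defines an unexpected reaction by nature or severity, so a labelled reaction of unlisted severity could be shown by preferred term, and ADRs, SAEs and SADRs are tabulated separately.

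Nor is laboratory safety reduced to one judged category. Section 11.2.5 adds a before-and-after McNemar comparison, abnormal results can count as AEs under section 10.4.1, and HbA1c and glucose are analysed as continuous changes.

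Finally, table detail is commonly left to the statistical analysis plan, which is not at hand. That answers requests for laboratory shift tables or an analysis of AEs leading to discontinuation. It does not answer the main point, because the aim and the test are both set in the protocol and the analysis plan cannot change the wording of section 3.1.

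**Conclusion.** The concern holds in a limited form. The safety aim in section 3.1 goes beyond the objective in section 4 and cannot be met by the test in section 11.2.5, since non-significance there is likely even when 20 mg carries a materially higher risk. For a true doubling, the chance of a non-significant result at 124 per arm is about 85%, 68% and 40% from base rates of 2%, 5% and 10%, and higher with Fisher's exact test. These figures rest on assumed AE rates and on every enrolled subject taking at least one dose; fewer subjects would raise them. The restriction of preferred terms to unexpected AEs is a secondary weakness. The change is worth making because it alters what the trial may claim about safety. It leaves the endpoints, analysis sets, sample size and primary conclusion as they are.

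**What to change.** - **Section 3.1:** replace the aim of demonstrating no significant difference with one that matches section 4, namely to estimate and describe the difference in AE incidence between the two doses.
- **Section 11.2.5 and the synopsis:** report the risk difference with a 95% confidence interval for any AE, any ADR and any SAE. State that a non-significant test will not be read as showing similar safety. The chi-square and Fisher tests may stay as descriptive output.
- **Secondary:** tabulate all AEs by SOC and preferred term, not only the unexpected ones.

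If the sponsor wants a formal claim of similar safety, it needs a justified margin and a sample size to match, which on the illustration above would exceed the planned enrolment. Estimation is the proportionate route.

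The cost is a change of wording and a few tables from data already collected, with no change to the sample size or visits. The real price is a more modest safety statement. Laboratory shift tables and an analysis of AEs leading to discontinuation are optional additions for the statistical analysis plan and not corrections of an error.
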